# Efficacy and safety of Shugan Jieyu Capsule in the treatment of depressive state after acute coronary syndrome: study protocol for a multicenter randomized controlled trial

**DOI:** 10.3389/fpsyt.2025.1683736

**Published:** 2025-10-16

**Keywords:** Shugan Jieyu Capsule, acute coronary syndrome, depressive state, randomized controlled trial, protocol

## Abstract

**Objective:**

This study aims to evaluate the efficacy and safety of Shugan Jieyu Capsules (SGJY) in patients with depressive state after Acute Coronary Syndrome (ACS).

**Methods:**

This is a multicenter, randomized, double-blind, placebo-controlled clinical trial. A total of 148 patients with depressive state after ACS recruited from five research centers, will be randomly assigned to either the SGJY group or the placebo group at a 1:1 ratio. In addition to standard therapies for ACS, the SGJY group will receive SGJY while the placebo group will receive a matching placebo. All participants will undergo 12 weeks of treatment, followed by 36 weeks of follow-up.

**Results:**

The primary outcome is the Hamilton Depression Rating Scale (HAMD-17). Secondary outcomes include major adverse cardiovascular and cerebrovascular events (MACCE), Seattle Angina Questionnaire (SAQ) score, depression and anxiety scales, the Short Form-36 (SF-36) health survey, Montreal Cognitive Assessment (MoCA) score, inflammatory cytokine levels, hypothalamic-pituitary-adrenal (HPA) axis activity, and brain-derived neurotrophic factor (BDNF) levels. Safety will be evaluated based on safety indicators and recorded adverse events. Additionally, metabolomic analysis will be conducted on patient serum samples collected before and after treatment to elucidate the potential metabolic pathways of SGJY ameliorates subthreshold depression after ACS.

**Conclusion:**

This trial will evaluate the efficacy and safety of SGJY in managing depressive state after ACS. Additionally, the potential of SGJY to improve long-term prognosis in patients with depressive state after ACS will be assessed.

## Introduction

1

Cardiovascular disease remains the leading cause of death worldwide, with acute coronary syndrome (ACS) being one of the most prevalent and life-threatening manifestations (1). Despite administering secondary prevention according to guidelines, the risk of recurrent coronary events remains as high as 32.5% within 2 years after discharge, with a 5-yearcardiovascular mortality rate of 11.2% (2). Notably, ACS-related hospitalizations account for the largest proportion (38.6%) of total cardiovascular-related healthcare expenditures (3). Furthermore, studies have shown that over 20% of patients experience depression after acute myocardial infarction (4), which increases the risk of major adverse cardiovascular events by 51% (5) in individuals with coronary artery disease, imposing a substantial economic burden on both families and society (6).

The American Heart Association (AHA) and European Society of Cardiology (ESC) guidelines recommend routine depression screening and appropriate therapeutic management for all individuals with cardiovascular disease (7, 8). While selective serotonin reuptake inhibitors (SSRIs) are considered first-line pharmacological agents for treating depression after ACS, their ability to reduce cardiovascular adverse events in patients with comorbid ACS and depression remains uncertain (9, 10). In addition, long-term use of SSRIs may cause varying degrees of side effects and drug resistance (11, 12), leading to reduced quality of life and poor treatment adherence.

Traditional Chinese medicine (TCM), known for its multi-component, multi-target, and multi-pathway synergistic effects, is commonly used as an adjunctive therapy. Shugan Jieyu Capsules (SGJY), the first Chinese patent medicine approved in China for the treatment of mild to moderate depression, is a nationally second-class protected TCM formulation composed of two herbs: *Hypericum perforatum* and *Acanthopanax senticosus*. Existing clinical evidence suggests that SGJY may alleviate symptoms in patients with coronary heart disease comorbid depression, with relatively mild adverse effects. However, the overall quality of the evidence remains low, as it primarily focuses on changes in depression rating scales while devoting limited attention to cardiac function and long-term outcomes (13). Furthermore, most previous clinical studies have focused on changes in depression rating scales. To address this gap, we designed a multicenter, randomized, double-blind, placebo-controlled clinical trial to assess the effects of SGJY on patient with depressive state after ACS. Specific efficacy indicators including quality of life, long-term cardiac prognosis, cardiopulmonary function, serum inflammatory markers, hypothalamic-pituitary-adrenal (HPA) axis-related hormones, and brain-derived neurotrophic factor (BDNF). The study will also explore the underlying mechanisms of SGJY in treating depressive state after ACS through metabolomic analysis.

## Materials and methods

2

### Design and settings

2.1

This is a multicenter, randomized, double-blind, placebo-controlled clinical trial. The trial was registered on the National Medical Research Registration and Filing Information System (www.medicalresearch.org.cn) on June 19, 2024 (Registration No. MR-11-24-037476), and on the International Traditional Medicine Clinical Trial Registry (itmctr.ccebtcm.org.cn) on June 1, 2024 (Registration No. ITMCTR2024000099). All documents, including the study protocol, informed consent forms, and case report forms (CRFs), comply with the Declaration of Helsinki and have been reviewed and approved by the Xiyuan Hospital Ethics Committee of the Chinese Academy of Medical Sciences (approval number: 2024XLA062-3). The clinical trial protocol follows the SPIRIT 2025 statement (14). The trial will be conducted in accordance with the Good Clinical Practice (GCP) Guidelines (2020) and reported according to the CONSORT 2025 statement (15).

Patients will be recruited from five centers in China: Xiyuan Hospital, China-Japan Friendship Hospital, the Eighth Affiliated Hospital of Sun Yat-sen University, the Third People’s Hospital of Fujian Province and Xuzhou City Hospital of TCM. A total of 148 participants will be enrolled after providing written informed consent. Participants will be randomly assigned in a 1:1 ratio to receive either SGJY or placebo, with a 12-week treatment period followed by a 36-week follow-up. A schematic diagram of the study procedures is presented in **Figure 1**.

**Figure 1 f1:**
[figure not shown]
Flow chart of the study design. ACS, Acute Coronary Syndrome; ACEI, angiotensin-converting enzyme inhibitor; ARB, angiotensin receptor antagonist; SGJY, Shuganjieyu Capsule; HAMA-17, Hamilton depression rating scale; MACCE, Major adverse cardiovascular and cerebrovascular events; SAQ, Seattle angina questionnaire; PHQ-9, Patient health questionnaire-9; HAMA, Hamilton Anxiety Scale; GAD-7, Generalized anxiety disorder-7; DARS, Dimensional Anhedonia Rating Scale; SF-36, Short form 36 health survey; MoCA, Montreal cognitive assessment; CPET, cardiopulmonary exercise testing; IL-1β, Interleukin 1 beta; IL-6, Interleukin 6; GDF15, Growth differentiation factor 15; sCD40L, Soluble CD40 ligand; CRF, Corticotropin-releasing factor; ACTH, Adrenocorticotropic hormone; BDNF, Brain-derived neurotrophic factor; TnI, Troponin I; TnT, Troponin T; ECG, Electrocardiogram; AEs, Adverse events; SAEs, Severe adverse events; FAS, Full analysis set; PPS, Per protocol set; SAS, Safety analysis set.

### Study population

2.2

#### Diagnostic criteria

2.2.1

The diagnostic criteria for ACS derived from the *2023 ESC Guidelines for the Management of Acute Coronary Syndromes* (16), while the diagnostic criteria for depressive state is drawn from the *Expert Consensus on the Diagnosis and Treatment of Anxiety, Depression, and Somatization Symptoms in General Hospitals* (17).

#### Inclusion criteria

2.2.2

Patients who eligible for the trial must fulfill all of the following criteria at the time of randomization:

Participants are aged between 18 and 75 years.A confirmed diagnosis of ACS within 2 to 12 weeks prior to enrollment, with hemodynamic stability and absence of acute cardiovascular complications.Participants exhibited persistent symptoms of depressed mood or anhedonia for at least 2 weeks, with 17 < HAMD-17 ≤ 24All eligible participants must provide written informed consent.

Note:

Depressed Mood: The affective manifestation persists nearly daily for the majority of waking hours, manifesting through either subjective affective experience (e.g., persistent feelings of sadness, emotional emptiness, or hopelessness) or objective behavior observed by others (e.g., frequent episodes of tearfulness).Anhedonia: Present almost daily occurrence for most of the day. This involves a significant decrease in interest or pleasure in all or almost all activities (which can be either self-reported or observed).

#### Exclusion criteria

2.2.3

Potential participants meeting any of the following criteria will be excluded from this trial enrollment:

Patients with impaired liver function (serum alanine aminotransferase or aspartate aminotransferase greater than 1.5 times the upper limit of normal value), impaired renal function (serum creatinine or blood urea nitrogen greater than the upper limit of normal value);Patients with severe hematologic disorders, malignant tumors, malignant arrhythmias, pulmonary edema, severe aortic valve stenosis, severe anemia;Patients with a history of depression or psychiatric disorders preceding the onset of ACS, or with marked suicidal ideation;Patients with heart failure classified as New York Heart Association (NYHA) class III-IV, left ventricular ejection fraction (LVEF) <35%, or those requiring mechanical circulatory support;Patients who have taken antidepressants or medications containing *Acanthopanax senticosus* or *Hypericum perforatum* chronically or within the past 4 weeks;Pregnant or lactating women, or those planning to conceive;Patients with autoimmune diseases (e.g., rheumatoid arthritis, ankylosing spondylitis, and inflammatory bowel disease) or taking immunosuppressive drugs within the last three months;Patients with acute infections in the past 4 weeks, or those showing signs or symptoms of infection (e.g., fever, cough, dyspnea, leukocytosis);Patients who have participated in or are currently enrolled in other clinical trials within the past 3 months;Patients with known hypersensitivity to any component of the study drug.

#### Termination and dropout of trial patients

2.2.4

Patients who fail to meet the inclusion criteria or fulfill any exclusion criteria.Patients with poor protocol compliance or who withdrew prematurely from the trial.Patients with incomplete medical records that hinder the evaluation of efficacy and safety.Patients whose condition deteriorated rapidly during the study, including those with acute cardiovascular events or malignant neoplasms.Patients whose depression worsens during the trial (HAMD-17 score >24 for over two weeks) or who display suicidal ideation.Patients with serious adverse events during the trial.Voluntary withdrawal by the patient.

#### Handling of dropout cases

2.2.5

After a trial participant drops out, researchers should maintain contact with them through means including phone calls, scheduled check-ins, follow-up visits, or written correspondence, inquire about the reasons for dropout, document the last dose administration time, and complete any feasible assessments.All selected trial participants, regardless of whether they drop out, should have their research-related medical records properly documented.

### Randomization, allocation concealment, and blinding

2.3

#### Random allocation

2.3.1

All eligible patients who provide informed consent will be randomly assigned in a 1:1 ratio to either the control group or the SGJY group. Stratified block randomization will be used, with clinical research center as the stratification factor. A statistician independent of trial analysis will generate the randomization table using SAS software, based on the stratification factor and allocation ratio. The number of blocks, block length, random seed parameters, and other confidential data will be sealed along with the randomization table in an opaque envelope, which will serve as the First unblinding record.

#### Blinding

2.3.2

This study adopts a double-blind design. The first level blinding corresponds to the group codes linked to medication numbers (Group A, Group B), while the second level pertains to the treatments assigned to each code (SGJY group or placebo control group). Both levels of blinding will be documented by statisticians independent of trial analysis. Two sealed copies of the blinding records will be maintained separately by the principal research center. These blinding records must remain unopened throughout the study period. The first unblinding for the statistical analyst will conduct after data lock, and the second after completion of the statistical analysis. Emergency envelopes may only be opened in the event of a medical emergency (serious adverse event, rapidly deteriorating condition). Each envelope will contain designated fields for the signature, date, and reason for unblinding by the person who opens it. Cases withdrawn due to therapeutic reasons should not be unblinded. The unblinded case materials must be kept intact.

#### Sample size calculation

2.3.3

The sample size was calculated based on the response rate of HAMD-17 score reduction, the primary efficacy endpoint. Based on existing literature, the response rate of HAMD-17 score reduction is 45.7% (18) in the control group and 69% in the Shu Gan Jie Yu group (19). Assuming a two-sided significance level (α) of 0.05 and power (1−β) of 80%. The ratio of the two sample sizes is 1. Thus, a sample size of 67 participants per group is required. Allowing for a maximum dropout rate of 10%, the sample size was increased to 74 per group, for a total enrollment of 148 participants.

### Interventions

2.4

The investigational drug (SGJY) and placebo are capsule formulations provided by Sichuan Jishengtang Pharmaceutical Co., Ltd. (Pengzhou, China). The composition of SGJY includes *Hyperic perforated herba, Acanthopanax senticosi radix et rhizoma seu caulis* (**Table 1**). SGJY and placebo capsules are identical in packaging, color, shape, and flavor, ensuring that neither participants nor investigators can distinguish the group allocation prior to unblinding.

**Table 1 T1:** The composition of Shuganjieyu Capsule (intervention drug).

Chinese name	Scientific name	Latin name	Species name
Guan ye jin si tao	Hypericum perforatum L.	*Hyperic perforated herba*	Garcinia
Ci wu jia	Acanthopanax senticosus (Rupr.et Maxim.) Harms	*Acanthopanax senticosi radix et rhizoma seu caulis*	Ginseng

#### Standard medical management

2.4.1

In accordance with current ACS treatment guidelines (20), participants will receive standard therapy, including antiplatelet agents, statins, and anti-ischemic medications (e.g., β-blockers, long-acting nitrates, calcium channel blockers). The type and dosage of medications administered to each patient will be documented in the case report form (CRF).

#### Experimental group

2.4.2

Participants in the experimental group will receive SGJY in combination with standard medical therapy. The dosage regimen is 0.36 g per pill, two pills orally, twice daily. The treatment period will last for 12 weeks. Participants will be instructed to return any unused medication and packaging at each visit to assess adherence.

#### Control group

2.4.3

Participants in the control group will receive placebo capsules. The dosage regimen of the placebo will match that of the SGJY group.

#### Drugs combined and contraindicated in trial

2.4.4

During the trial, the use of other traditional Chinese medicine (TCM) decoctions, oral or intravenous TCM patent medicines, or TCM-based therapies (e.g., acupuncture or cupping), as well as paroxetine, sertraline, and other drugs that may interfere with depressive state after ACS, will be prohibited. Adjunctive treatments for depression, such as psychological counseling and supportive psychotherapy, are prohibited as well. Concomitant treatment for comorbidities is permitted during the trial. However, all concomitant treatments must be documented in CRF, including the medication (or therapy) name, dosage, frequency, and treatment duration.

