##### Primary outcome

2.5.2.1

The Hamilton Depression Rating Scale (HAMD-17) will be evaluated at each visit. The primary outcome is the proportion change in patients with a reduction rate more than 50% or a HAMD-17 score of less than 7 after 12 weeks of treatment. The reduction rate will be calculated using the following formula: [(baseline score - score at week 12)/baseline score] × 100%. The efficacy index is classified into three categories: cured (HAMD-17 score < 7), effective (reduction rate > 50%), and ineffective (reduction rate < 50%). The overall response rate is calculated as: [(cured cases + effective cases)/total cases] × 100%.

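### The ban on antidepressants, counselling and psychotherapy has no end week and, read literally, runs to week 48, 36 weeks after the last dose and after the primary endpoint

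*Protocol article*

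**What the plan says.** - **The ban.** Section 2.4.4 opens with "During the trial, the use of other traditional Chinese medicine (TCM) decoctions, oral or intravenous TCM patent medicines", continues the list to paroxetine, sertraline and other drugs that may interfere with the depressive state, and then adds "Adjunctive treatments for depression, such as psychological counseling and supportive psychotherapy, are prohibited as well". The second sentence has no time limit of its own and takes over that of the first.
- **Dosing.** Section 2.4.2: "The treatment period will last for 12 weeks". Section 2.1 describes the design as one "with a 12-week treatment period followed by a 36-week follow-up". Table 2, the trial schedule, has its last visit (V7) at week 48.
- **Primary outcome.** Section 2.5.2.1 counts patients with "a reduction rate more than 50% or a HAMD-17 score of less than 7 after 12 weeks of treatment".
- **Entry.** Section 2.2.2: "Participants exhibited persistent symptoms of depressed mood or anhedonia for at least 2 weeks", with HAMD-17 above 17 and at most 24.
- **Exit for depression.** Section 2.2.4 lists "Patients whose depression worsens during the trial (HAMD-17 score >24 for over two weeks) or who display suicidal ideation". It also lists poor compliance with the protocol and voluntary withdrawal.
- **Follow-up after a change.** Section 2.8 asks investigators to record a modified regimen and carry on with planned follow-up, and to follow participants to the end of the study.

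**The concern.** The article has a term for the 12 weeks on drug and uses it elsewhere, but section 2.4.4 refers to the trial as a whole. A site that follows the text would withhold antidepressants, and even counselling, from a patient who is still depressed at week 12, has stopped study drug and has already contributed to the primary analysis. For the 36 weeks that follow, the restriction does nothing for the primary endpoint.

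The article itself gives the reason this matters for patients. Its Introduction cites cardiology guidelines that "recommend routine depression screening and appropriate therapeutic management for all individuals with cardiovascular disease", and its Discussion accepts that some participants may meet criteria for major depressive disorder. Retention is also at stake. If withdrawal is the price of treatment, patients may leave who would otherwise have stayed for the week-48 scales and the MACCE record. Five centers could also apply the undefined end date differently.

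**Working it through.** **1. Length of the ban, read literally.** Trial length is 12 + 36 = 48 weeks (section 2.1, Table 2). Weeks after the last dose: 48 − 12 = 36. Share off drug: 36/48 = 75%.

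**2. Can an unchanged patient leave through the worsening rule?** HAMD-17 takes whole numbers, so entry means 18 to 24 (section 2.2.2). The exit needs more than 24 for over two weeks, or suicidal ideation (section 2.2.4). The ranges do not overlap, so an unchanged patient without suicidal ideation does not qualify. What remains is voluntary withdrawal, or starting a banned treatment and risking the poor-compliance ground.

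**3. The plan's own figure.** Section 2.3.3 plans on response rates of 45.7% (control) and 69% (SGJY), two-sided 5% significance level, 80% power. With unpooled variances:

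n = (1.960 + 0.842)² × [0.457 × 0.543 + 0.69 × 0.31] / 0.233² = 66.8, rounded up to 67 per group.

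Then 67 × 1.1 = 73.7, rounded up to 74. The stated 67 and 74 are reproduced, and none of this depends on what happens after week 12.

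**4. Upper bound on patients affected.** Week-12 non-responders at those rates:

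| | Placebo | SGJY | Total |
|---|---|---|---|
| 74 per group | 74 × 0.543 = 40.2 | 74 × 0.31 = 22.9 | 63.1 of 148 (42.7%) |
| 67 per group | 67 × 0.543 = 36.4 | 67 × 0.31 = 20.8 | 57.2 of 134 |

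Non-response is wider than unchanged. A reduction of no more than 50%, with a score of at least 7, means 9 or more from a baseline of 18, and 12 or more from a baseline of 24. Some of the 63 are therefore mildly ill and below the entry threshold, and some may exceed 24 and exit. The article gives no number for patients still at 18 to 24.

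**5. How many might start treatment (assumption).** If a share f of non-responders would take treatment once allowed, starts number 63.1 × f: 6.3, 15.8 and 31.6 patients for f = 10%, 25% and 50%.

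**6. What lifting the ban costs the long-term comparison (assumption).** Suppose a share r of those starting treatment respond, f and r are equal in both arms, and week-12 status otherwise persists. Each arm's response becomes p + (1 − p)fr, so the planning difference of 69 − 45.7 = 23.3 points becomes 23.3 × (1 − fr).

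| | f = 10% | f = 25% | f = 50% |
|---|---|---|---|
| r = 25% | 22.7 | 21.8 | 20.4 |
| r = 50% | 22.1 | 20.4 | 17.5 |

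The relative loss is 2.5% to 25%. Response is defined only at week 12, so this is illustrative.

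**The case against.** **The authors may have meant only the treatment period.** The rule sits under Interventions, before the follow-up section, and the article uses time terms loosely: section 2.4.5 calls the on-drug visits post-treatment. The full protocol may fix the end date. This stands as a doubt about intent, and it makes the harm conditional. It does not remove the point, because the article does state a scope, and that scope is the whole trial.

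**The ban protects a stated aim.** Long-term prognosis is an objective, with HAMD-17 and MACCE followed to week 48. Lifting the ban trades some of that contrast for patient care. This is fair, although the article does not give it as the reason. The affected comparisons are secondary and can still be interpreted as regardless of later treatment.

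**Patients can withdraw, and follow-up is meant to continue.** Both are true. Neither lifts the ban, and the poor-compliance ground in section 2.2.4 pulls against the follow-up rule in section 2.8.

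**Stronger readings that a reader might infer, and that the documents do not support:**

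- That patients are in fact denied care for 36 weeks. This depends on the literal reading.
- That about 63 patients would be stuck at their entry score. That count includes every non-responder, with scores from 9 upward.
- That the exit above 24 is itself a defect. A worsening rule need not remove unchanged patients.
- That all TCM should be freed after week 12. The patient-care argument concerns depression treatment only.
- That follow-up ends when a patient starts treatment. No section says so.

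**Conclusion.** The point holds as a fault of scope. As worded, section 2.4.4 bars antidepressants, counselling and psychotherapy to week 48, which is 36 weeks (75% of the trial) beyond the last dose and beyond the primary endpoint. A patient still at 18 to 24 has no worsening exit. This rests on the literal reading. If only the treatment period was meant, the same correction is needed as a clarification.

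The number of patients concerned is unknown. About 63 of 148 is an upper bound that assumes the planning response rates and no dropout. It should be fixed for patient care and retention. Confidence is medium because the intent is uncertain.

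**What to change.** 1. **Section 2.4.4.** Limit the ban on antidepressants, counselling and psychotherapy to the 12-week treatment period, for example: *From randomization until the week-12 assessment is complete, antidepressants, counselling and psychotherapy for depression are not permitted; afterwards they are permitted and recorded.* The ban on SGJY, its component herbs and other TCM may stay to week 48 if the sponsor wants to protect the long-term contrast, but the text should then say so.
2. **Section 2.2.4.** Add: *Starting depression treatment after week 12 is not a ground for termination; the participant is followed to week 48.* This agrees with section 2.8.
3. **Reporting.** Use the concomitant-treatment records already taken at V5 to V7 to report starts by arm, with type and week, and describe outcomes at weeks 24 to 48 as comparisons regardless of later treatment.

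The cost is a few sentences of wording, with no new visits, staff or data items. The downside is some dilution of the secondary long-term comparisons, sized above under labelled assumptions. Keeping the TCM ban avoids the further risk of placebo patients taking marketed SGJY.
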